### Recruitment {15}

Schools will be enlisted through existing contacts (see Acknowledgements), school consortiums, mental health and wellbeing leads and senior management teams and Local Clinical Research Networks (LCRN) across the UK. Due to the ongoing COVID-19 pandemic restrictions, all meetings with contacts will occur online via Microsoft ® Teams.

Interested schools will sign a site agreement and nominate a key member of staff to work with the research team to promote and engage families. The research team will be guided by individual schools as to the most appropriate way of engaging families. These will include distribution of promotional materials (posters/information leaflets, see Additional file 1) via school intranet, communication app and/or email. Parents/carers and young people will also be able to register directly for the trial through the wider community. Trial information and a link to the trial will be distributed via University of Warwick social media (Twitter and Facebook) and family/parenting groups and charities in the UK to allow for this. Those interested in participating will be asked to register for the trial and provide consent for their and their child’s participation on the dedicated trial database. They will also provide contact details for their child.

## Assignment of interventions

### Sequence generation {16a}

Allocation to trial arms will be implemented using WCTU’s automated minimisation procedure within the PIPA trial database. This adaptive stratified sampling method will minimise imbalance between number of participants in each intervention group [63].

### Concealment mechanism {16b}

Allocation will be concealed until selection criteria for entry into the trial have been met. This will be implemented, maintained and electronically revealed by WCTU.

### Implementation {16c}

Allocation will be 1:1 ratio between intervention and active control.

## Assignment of interventions: blinding

### Blinding {17a}

The Chief Investigator (CI) and Health Economist will be blinded after assignment to intervention. The Statistician, Assistant Professor, Research Associate, Senior Project Manager and Trial Manager (TM) *will not* be blinded to allocations.

### Procedure for un-blinding if needed {17b}

The Data Monitoring Committee (DMC) will have access to un-blinded, aggregate, comparative data. Un-blinding will not occur until all decisions on data evaluability have been documented.

##### Secondary outcome measures

ParentingParenting to Reduce Adolescent Depression & Anxiety Scale (PRADAS [45]) and The Parental Self-Efficacy Scale (PSES [46])

The PRADAS assesses parental concordance with a range of evidence-based parenting guidelines for the prevention of depression and anxiety across nine domains: *parent-child relationship*, *involvement*, *relationships with others*, *family rules*, *home environment*, *health habits*, *dealing with problems*, *coping with anxiety* and *professional help-seeking*. Reliability, test-retest reliability and convergent validity of the PRADAS have been supported by moderate to high correlations with established parenting measures [45].

The PSES was developed to measure parenting self-efficacy in behaviours that may reduce adolescent risk for depression and anxiety. It utilises a Likert-type scale to assess parental confidence in carrying out behaviours related to the nine domains assessed by the PRADAS and is administered in conjunction with the PRADAS. The PSES has been found to have high reliability and construct and convergent validity [46]. The PRADAS and PSES will be completed by parents/carers at baseline, 6 months and 15 months.

Parental mental wellbeingThe Short Warwick-Edinburgh Mental Wellbeing Scale (SWEMWBS [49])

The SWEMWBS is a mental wellbeing measure for use with a wide range of populations. It consists of seven positively worded items rated on a Likert-type scale. It has shown good content validity with high test-re-test reliability (0.83 [66]). It will be completed at baseline, 6 months and 15 months.

Adolescent resilienceThe Difficulties in Emotional Regulation Scale - Short Form (DERS-SF [53])

Developed from the original DERS [67], this scale assesses emotional regulation problems in adults and adolescents. It consists of six sub-scales, each with three items: *limited access to emotion regulation strategies*, *non-acceptance of emotional responses*, *difficulty with impulse control*, *difficulty engaging in goal-directed behaviour*, *lack of emotional awareness* and *clarity*. Confirmatory analysis found similar correlation patterns to full DERS measure, ranging from 0.90 to 0.98, sharing 81–96% variance [53]. The DERS-SF will be used to assess resilience of adolescents and will be completed at baseline, 6 months and 15 months.

Adolescent anxietyThe Children’s Anxiety Scale-8 (CAS-8 [55])

##### Health-related quality of life

AdolescentThe Child Health Utility Index 9D (CHU-9D [58]) and EuroQol 5 Dimensions Youth 5 (EQ-5D-5L-Y [59])

These are generic measures of health-related quality of life in children and will be completed by adolescents at baseline, 6 months and 15 months. The CHU-9D assesses children’s functioning on the day across nine domains: *worry*, *sadness*, *pain*, *tiredness*, *annoyance*, *school*, *sleep*, *daily routine* and *activities*. The EQ-5D-5L-Y requires respondents to report their health on five different dimensions (*mobility*, *self-care*, *usual activities*, *pain/discomfort* and *anxiety/depression*) with five severity levels and rate their overall health using a visual analogue scale.

Parent/carerEuroQol 5 Dimensions 5 Level (EQ-5D-5L) and EQ-5D-5L-Y proxy [52]

Completed by parents/carers at baseline, 6 months and 15 months, the EQ-5D-5L is a self-report of their own health whilst the proxy measure is regarding their child’s health.

Data will be converted into health utilities using established utility algorithms to estimate family dyad quality-adjusted life years (QALYs; see Health Economic Analysis). The QALY is a measure of health outcome incorporated into cost-effectiveness analysis intended to aid decision-makers charged with allocating scarce resources across competing healthcare programmes and is required by the National Institute for Health and Care Excellence in England and Wales for health technology assessment.

Parent/carer estimates of resource utilisationThe Client Service Receipt Inventory (CSRI)

This is a bespoke measure of health, social care and education-related resource use over the trial follow-up period. It covers *hospital care*, *community-based health and social services use*, *medication use*, *private health care*, *school absence*, *special educational needs and other support*, *time off work by parents* and *other expenses* and will be completed by parents/carers at baseline, 6 months and 15 months.

### Plans to promote participant retention and complete follow-up {18b}

Based on evidence that incentives may increase rate of assessment completion [70], each participating family will be offered a £25 voucher following completion of all baseline and follow-up assessments.

Automated weekly emails and fortnightly check-in calls, alternated with a text message, will be made by the research team to help maintain engagement. Calls will *not* offer parenting advice.

Links to the online PIPA database will be sent by email and/or text to parents/carers and adolescents for completion of follow-up assessments.

### Data management {19}

The University of Warwick will act as data controller for the trial. Informed consent and assent forms will be held electronically at WCTU following Data Management and Security SOPs.

Access to personal/confidential data will be monitored throughout the trial and restricted to those delegated roles by the CI.

Monash University will be the data processor for the trial and will maintain the ‘Partners in Parenting’ website which houses the interventions, baseline PRADAS and PSES questionnaires. All data will be stored after generation on a Google Cloud Platform, via the European Data Centre. Pseudonymised data will be transferred to the University of Warwick and stored in the same manner as other trial data.

The text and email messaging company Twilio© will be utilised to communicate with participants with access to participant names, email addresses and mobile phone numbers. Selected staff from Clinical Research Networks providing phone-call support will have limited access to these and limited intervention data in order to complete fortnightly check-in calls. Some anonymized questionnaire data will be transferred for scoring purposes. Appropriate contracts are in place for these purposes.

Storage and transfer of data throughout the trial will be done in accordance with University of Warwick data policies and standard operational procedures. WCTU will archive trial documentation and data for at least 10 years after completion of the trial.

### Confidentiality {27}

Any personal data will be handled and stored in accordance with the 2018 Data Protection Act held securely at WCTU until the end of the trial and disposed of in accordance with WCTU procedures. Participants will be given unique trial identification numbers to maintain anonymity. The need for personal details, necessary for phone calls and texts is clearly documented in participant information sheets (see Additional file 1). Personal identifying information for ineligible families and those wishing to withdraw will be deleted at the end of the trial as per WCTU SOPs.

Data will only be accessible by the PIPA research team using assigned logins and passwords. All data will be treated in confidence and not disclosed or used for any unrelated purposes (except by prior agreement with the participant or to address specified risks to the participant, researcher or others throughout the trial).

## Statistical methods

### Statistical methods for primary and secondary outcomes {20a}

All analyses will be performed on an intention-to-treat basis (ITT). The ITT population will comprise all randomised participants. Baseline characteristics will be presented using descriptive statistical methods; continuous variables will be summarised using means and standard deviations and skewed continuous variables using median and inter-quartile range. Categorical data will be summarised using frequencies and percentages. Outliers will be identified using graphical methods. Participant flow throughout the trial including numbers screened, recruited, randomised, and withdrawn will be documented using a CONSORT diagram. Means and 95% confidence intervals for mental health and wellbeing, as assessed by primary and secondary outcomes, will be summarised at baseline, 6 months and 15 months post-randomisation.

The primary outcome is change in parent-reported SMFQ score between entry to the trial and 15 months post-randomisation. This will be analysed using a linear mixed model, with school as a random effect and age group and number of participating parents as fixed effects. Cases of depression between trial entry and 15 months post-randomisation will be reported and appropriate models used to assess any difference between intervention arms. Linear mixed models will also assess impact of intervention on secondary outcomes.

### Interim analyses {21b}

There are no pre-planned interim analyses or formal rules for the full PIPA trial. The DMC will review emerging trial data and external evidence on an ongoing basis and may recommend early stopping, if appropriate, following stop/go criteria:

The study will have a pilot phase to establish the feasibility of the full PIPA trial. The stop-go decision will be made by the TMG, following consultation with the TSC and DMC 9 months from trial commencement using the following recruitment stop-go criteria as a guide:Go: More than 80% of the 128 dyads within 9 months since the first randomisation (February 2021)Discuss: Between 50 and 80% randomised. The trial team, the NIHR and the TSC should discuss and consider additional remedial strategiesStop: Less than 50% randomised. The trial could stop for lack of interest after discussions with the TSC and the NIHR

The stop/go criteria will be subject to review by the TSC/DMC in light of Covid-19 disruptions and any amendment will be notified.

### Methods for additional analyses {20b}

#### Sub-group and adjusted analyses

Separate analysis of primary outcome and effect estimates will be conducted for school location (proxy for social deprivation), parents’/carers’ highest educational level (surrogate for socioeconomic status) and ethnicity. All analyses will be adjusted by design variables (school, age group, gender of young person, gender of parent/carer and total number of parents accessing modules/factsheets).

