### Intervention description {11a}

#### Personalised programme

The personalised programme is delivered online via the ‘Partners in Parenting’ website [20]. The programme fulfills the principles of the evidence-based Persuasive Systems Design model, which uses technology to influence behaviour change [43]. Principles include tailoring, feedback, personalisation and self-monitoring, all associated with greater programme adherence [44]. Adaptations for a UK context were made following feedback from a series of adaptation focus groups with parents/carers, teachers and adolescents.

After assessment of current parenting practices using the ‘Parenting to Reduce Adolescent Depression and Anxiety Scale’ (PRADAS [45]) and the ‘Parental Self-Efficacy Scale’ (PSES [46]) parents/carers will receive individually tailored feedback and will be recommended up to nine modules (targeting the nine modifiable parenting domains) (see Fig. 2).

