#### Standard educational package

The active control is also delivered via the ‘Partners in Parenting’ website and consists of five factsheets (to match expected mean number of modules received by the intervention group; *n* = 5.2 [39]) *without* tailored, actionable strategies for parents/carers and released in a set order on a weekly basis. Factsheets were adapted from highly credible resources in Australia (Raising Children [47], as used by the Australian RCT. They were modified for a UK context following feedback from adaptation focus groups with parents/carers and teachers. Factsheets cover the following topics: (1) Teen development, (2) The teenager’s developing brain, (3) The teenager’s changing body, (4) Resilience, and (5) Happy teenagers and teenage wellbeing.

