#### Parents/carers

SMFQ data from a large population samples suggest that more than 20% of adolescents will report depressive symptoms [60]. Parents/carers of adolescents scoring ≥7 (indicative of elevated risk of depression and/or depressive disorder [61, 62]) will receive an automated message confirming eligibility. Families of those scoring <7 will be deemed ineligible and receive an automatically generated email or text informing them of this. Should they require further information or guidance, they will be directed to the list of helpful resources available on the PIPA trial website.

Whilst multiple parents/carers from the same family may participate in the programme, only one will be asked to complete baseline and follow-up measures. Baseline assessment of parenting practices (using PRADAS and PSES) will assess the nine modifiable parenting domains (see Fig. 2). Participants will then be randomly allocated to receive either the personalised programme or standard educational package.

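### The covariate meant to adjust all analyses is worded as parents accessing content, which is seen only after allocation, and it does not match the covariate in the primary model

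*Protocol article*

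**What the plan says.** Three parts of the protocol article bear on this point.

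- **Sub-group and adjusted analyses, under {20b}.** "All analyses will be adjusted by design variables". The bracketed list names school, age group and gender of the young person, and closes with "gender of parent/carer and total number of parents accessing modules/factsheets".
- **Statistical methods for primary and secondary outcomes {20a}.** The primary outcome goes into a linear mixed model "with school as a random effect and age group and number of participating parents as fixed effects". The two gender variables are not mentioned here.
- **Participant timeline {13}, Parents/carers.** "Whilst multiple parents/carers from the same family may participate in the programme, only one will be asked to complete baseline and follow-up measures". After the baseline assessment of parenting, "Participants will then be randomly allocated to receive either the personalised programme or standard educational package".

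The Intervention section describes what there is to access. In one arm parents "will be recommended up to nine modules", tailored to their answers and released weekly. In the other they get five factsheets in a fixed order, without tailoring. Trial design {8} and section {20a} both commit to intention to treat. Sequence generation {16a} describes minimisation but lists no factors.

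**The concern.** A covariate in a randomised comparison should be fixed before allocation, or at least be something allocation cannot change. A count of parents who access modules or factsheets does not meet that test as worded. Before allocation a family has neither, and afterwards each arm has different material. Whether a second parent logs in may depend on what the family was given.

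If it does, conditioning on the count does two things. It removes any benefit that runs through a second engaged parent, which is part of the total effect the trial sets out to estimate. It also compares families that reached the same count under different offers. If cohesion or motivation drives both access and the child's score, those families are no longer alike. In neither case is the result the intention-to-treat effect, and a larger sample does not help.

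The two sections also name different covariates for what should be the same adjustment, so two analysts following the article could fit different primary models.

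**Working it through.** **1. The plan's own figure.** Inputs from Sample size {14}: difference 0.35 SD, pre-post correlation 0.5, power 90%, 5% level (two-sided assumed, since sidedness is not stated), 20% loss. Allocation is 1:1.

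- SD of change = √(2 × (1 − 0.5)) = 1 in units of the score SD.
- A two-sample t-test needs 172.5, so 173 per arm and 346 in total.
- 346 / 0.80 = 432.5, so 433.

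Both stated figures are reproduced. The covariate question does not alter them.

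**2. Order of events.** Baseline assessment, then allocation, then weekly release of content by arm. Access to that content can only be recorded in the last step. No section says when the number of parents is recorded.

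**3. Size of the shift.** In a linear model with arm and the access count, least squares gives

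unadjusted effect = adjusted effect + γ × Δ,

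where Δ is the difference between arms in mean number of parents accessing and γ is the association of one more accessing parent with outcome, given arm. The adjusted estimate therefore moves by γ × Δ, and is unmoved if either is zero. γ covers both routes in the concern: a true effect of the second parent and a shared family cause.

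The article gives neither Δ nor γ. The values below are assumptions. Δ is taken as a difference in the share of families with a second parent accessing, and γ as SD lower SMFQ. Power is for a two-sample t-test with 173 per arm and residual SD held at 1.

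| Δ (points) | γ (SD) | Shift (SD) | 0.35 becomes, if access is higher in the intervention arm | Power | 0.35 becomes, if access is lower in the intervention arm | Power |
|---|---|---|---|---|---|---|
| 0 | any | 0 | 0.35 | 90% | 0.35 | 90% |
| 5 | 0.2 | 0.01 | 0.34 | 88% | 0.36 | 92% |
| 10 | 0.3 | 0.03 | 0.32 | 84% | 0.38 | 94% |
| 15 | 0.4 | 0.06 | 0.29 | 77% | 0.41 | 97% |
| 20 | 0.5 | 0.10 | 0.25 | 64% | 0.45 | 99% |

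The higher power in the last column is no gain: it is the chance of rejecting on an effect that is overstated.

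**4. Simulation check.** The model had a true total effect of −0.35 SD, a count of 0, 1 or 2 parents accessing, and a family-engagement factor correlated 0.6 with the variable underlying access. That factor had a coefficient of 0 or −0.3 on outcome, and each accessing parent a direct effect of 0 or −0.2 SD.

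- No arm difference in access: no shift.
- Access differs but is unrelated to outcome given arm: no shift.
- Arms differ by about 0.16 parents and access is related to outcome: shift 0.03 to 0.07 SD towards zero (power about 73% to 84%), with the sign reversed when access is lower in the intervention arm.
- Arms differ by about 0.31 parents: shift 0.06 to 0.14 SD (power about 48% to 76%). This lies outside the 5 to 20 point range used in the table.

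**The case against.** The strongest reply is that the wording is loose and the intention sound. The other listed variables (school, age group, the two genders) are known at entry, and in a minimised trial design variables usually means allocation factors. Section {20a} speaks of "age group and number of participating parents as fixed effects", which a count declared at registration would satisfy without any bias. On that reading only the phrase about access needs tidying. The reading is possible, but nothing in the article says the number is recorded before randomisation.

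Scope can also be questioned. The sentence sits under additional analyses, directly after the sub-group sentence, and could be meant only for those. Its words nonetheless cover all analyses, and a sub-group estimate would be exposed in the same way.

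Against a difference in access, the article says five factsheets were chosen to match an expected mean of 5.2 modules. Both arms use the same website, weekly release, emails, calls and texts. The covariate counts parents, not modules, so the number of modules on offer bears on it only indirectly. This makes a large arm difference less likely but does not exclude one, since the content still differs in tailoring and interactivity.

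Finally, the larger assumed associations, 0.4 and 0.5 SD for one more accessing parent, exceed the whole effect the trial is powered to find. That is a fair reason to treat the lower rows of the table as extreme. Precise covariate definitions are often left to the analysis plan, but here the article does state a definition, and it is an unsuitable one.

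**Conclusion.** The point holds as a risk in the stated wording. Followed literally, the adjustment conditions on uptake observed after allocation, which conflicts with the intention-to-treat aim, and it disagrees with the covariate named for the primary model.

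A reader might infer that the primary estimate would be biased, or that the count cannot be an allocation factor. The article supports neither. Bias needs access both to differ by arm and to be related to outcome given arm, and no section shows either. Because the minimisation factors are not listed, a number of parents fixed at baseline could be among them. Nor can one infer that power will be lost, because the shift can go either way.

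The range of 0.01 to 0.10 SD in either direction, against 0.35, rests wholly on the assumed access differences and associations. The true figure may be zero.

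**What to change.** Use one covariate, in the same words, in section {20a} and in the section on sub-group and adjusted analyses: the number of parents/carers registered to take part, recorded before randomisation. If that number was not captured before allocation, drop the covariate from both. Report the number of parents who access modules or factsheets by arm, as an adherence or process measure only.

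The cost is a sentence in each of the two sections and the matching line of the analysis plan. No new data are needed, and the sample size stays at 346 evaluable and 433 recruited families.
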